## Abstract

**Background:**

Chronic obstructive pulmonary disease (COPD) is a respiratory condition characterised by dyspnoea, excessive sputum production, chronic cough, bronchitis and emphysema. Functionally, exercise tolerance is poor for people with COPD and is linked to difficulty in performing daily tasks. More specifically, exercise difficulties are due partly to dyspnoea and lower limb skeletal muscle dysfunction. The benefit of exercise that does not exacerbate the disease while improving exercise tolerance is salient. Whole-body vibration (WBV) is a mode of physical activity known to improve muscular function of the lower limbs, yet efficacy has not been investigated for a WBV intervention conducted in a home-based setting for people with COPD.

**Methods/design:**

This clinically registered trial is a non-randomised placebo cross-over intervention based in the home of each participant (ACTRN12612000508875). Participants diagnosed with COPD will complete a six-week WBV intervention and then after a two-week washout period, will complete a six-week placebo training intervention. Participants will complete sessions twice a week. The duration of the trial is 14 weeks. Community-dwelling older adults with COPD will provide informed voluntary consent to participate. Outcome measures will include immediate, acute, and long-term responses to exercise.

**Discussion:**

Quantifying responses to WBV among people with COPD will allow discussion of efficacy of WBV as a mode of physical activity. The skill required by the participant to perform physical activity with WBV is not demanding and may enhance habitual sustainability. The results of this trial could be used to support further research in both clinical and community settings.

**Trial registration:**

Australian New Zealand Clinical Trials Registry (ANZCTR12612000508875)

## Background

The World Health Organisation’s (WHO) current definition of chronic obstructive pulmonary disease (COPD) is a lung ailment fundamentally characterised by persistent blockage of airflow from the lungs [1]. In 2004 the WHO estimated 64 million global cases of COPD and later predicted COPD to become the third leading cause of death by 2030 [2]. Among Australians, COPD was the third leading cause of burden of disease and injury behind ischaemic heart disease and stroke [3]. Somewhat understandably, tobacco usage was listed with physical inactivity as the two leading risk factors eliciting burden of disease in Australia [3]. Although not always the case, tobacco smoke is the leading risk factor for COPD [4]. While the cost of COPD in Australia has not been directly estimated, respiratory disease alone accounted for AU$3.31 billon (6.3%) of the total allocated health expenditure in Australia [5].

Given that COPD diminishes the ability of the lungs to supply the body with oxygen, most modes of physical activity lead to breathlessness if the disease is progressed. Perceived breathlessness, or dyspnoea, leads to physical inactivity and consequently compounds the risk of burden of disease to those individuals. As a counteractive strategy, physical activity is routinely incorporated to the management of stable COPD [6].

Recommendations from the WHO, the American Thoracic Society, the European Respiratory Society and the Thoracic Society of Australia and New Zealand, and other professional bodies support physical activity as integral to pulmonary rehabilitation programs in public heath settings to assist individuals affected by COPD [6]. A goal of physical activity within pulmonary rehabilitation is to improve exercise tolerance for people with COPD. During physical activity, the cardiovascular and neuromuscular systems are stressed above resting levels, which if continued over time, can improve systemic responses. Specifically, an improvement of cardiac output and cellular respiration are common after physical activity interventions [7]. Improvement in exercise tolerance has functional benefit such as the increased ability to complete activities of daily living (ADLs).

Maintenance and improvement of ADLs is central for functional independence [6,8]. Given that functional independence can rely on the ability to complete ADLs, muscular strength, muscular power and gait ability are considered important. Activities requiring strong and powerful muscular contraction are fundamental and include rising from a chair, climbing stairs, turning and adjusting posture, and stumbling to avoid a fall. People with COPD have less muscular strength and power than healthy age matched controls [9]. Subsequently, this population may have poorer exercise tolerance associated with muscular weakness [10]. As such, for people with COPD, muscular deconditioning/dysfunction is postulated to lead to poor performance of ADLs and poor exercise tolerance.

A primary objective of pulmonary rehabilitation is to combat poor muscular performance. The components of pulmonary rehabilitation vary, but include physical activity (both aerobic conditioning and resistance training), healthy lifestyle education, and nutrition counselling [11]. Initially, pulmonary rehabilitation can be implemented at an outpatient setting, usually followed by a home-based intervention that relies mostly on the compliance of the patient. Efficacy was established after systematic review of both outpatient pulmonary rehabilitation [12-14] and home-based pulmonary rehabilitation [15-17].

During pulmonary rehabilitation, aerobic conditioning was most effective in improving exercise tolerance at intensities over 50% of peak oxygen consumption (VO_2peak_) [11,18]. Although resistance training improved muscular strength [19], muscular power [20] and variables of gait [21], dedicated strategies for resistance training of the lower limbs lack thorough condition specific recommendation for people with COPD. A recent literature review of resistance training during peripheral muscle training reported the efficacy of resistance training for people with COPD [8]. As such, resistance training of the lower limbs elicited appreciable gains in muscular strength for people with COPD that may carry over to performance of some ADLs [8]. However, resistance training was conducted in conjunction with other modes of physical activity such as aerobic conditioning. The independent effect of resistance training therefore, could not be established.

Considering the statistical and scientific evidence for efficacy of physical activity to reduce burden of disease, the need for safe and valid exercise interventions for people with COPD is salient. The common modes of physical activity; aerobic conditioning and resistance training can exacerbate the disease and affect program compliance [22,23] and may lead to reduced physical activity because of fear of breathlessness. The clinical and social merit of physical activity that can minimise dyspnoea may provide additional exercise tolerance benefit for people with COPD. Whole-body vibration may be such a mode of physical activity, and can be easily completed in the home with little skill demand.

Whole-body vibration is a mode of physical activity during which an individual stands on a vibration platform that can create acceleration predominantly in the vertical (Fz) direction. The accelerations are transmitted to the body and postulated to elicit physiological responses similar to other modes of physical activity such as aerobic conditioning and resistance training.

After WBV, increased leg muscular strength and muscular power [24,25], oxygen consumption [26,27], growth hormone, and testosterone levels [24,28] were reported in healthy young and older adult populations. Furthermore, WBV may be a safe and effective mode of physical activity to improve muscular strength, body balance and mechanical competence of bone for older adults with low bone mineral density [29,30]. A growing body of literature on the impact of WBV has included sub-optimal health populations such as cystic fibrosis [31], multiple sclerosis [32] and stroke [33]. Yet to date, well conducted trials into the efficacy of WBV in patients with COPD are scarce in the literature.

One paper has been published to investigate efficacy of WBV to improve muscular strength and muscular power of people with COPD. In conjunction with a clinically based three-week pulmonary rehabilitation intervention, WBV may have enhanced exercise tolerance [34]. The authors suggested that long-term studies are needed to determine optimal intensity and duration of WBV for people with COPD, though WBV seemed to be a promising new mode of physical activity [34]. However, efficacy of a standalone WBV intervention remains unknown in outpatient and home-based settings.

### Objective

The objective of the trial is to advance knowledge of effects of physical activity on exercise tolerance and functional performance of the lower limbs of people with COPD, and to test the efficacy of a WBV intervention to beneficially effect exercise tolerance and functional performance of the lower limbs without causing exacerbations. The intervention will be conducted and data collected in the home of each participant.

## Methods/design

This trial will be conducted as a non-randomised intervention with crossover to placebo. Given the nature of COPD, and exacerbations expected of it, this trial will be a phase II efficacy trial and as such will not be conducted as a randomised controlled trial. People with stable COPD will be invited to participate. It is necessary to first conduct the WBV intervention, and then the PLACEBO intervention in an effort to maximise participant numbers in the WBV group, with anticipated dropout over the course of the 14-week intervention. A control condition could compromise trial compliance and randomisation is not critical to an efficacy trial.

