### Interventions

Across the 14-week duration of the trial, participants will be first allocated to a six-week WBV intervention, a two-week washout period [37], and a six-week PLACEBO intervention.

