### Sample size

It is expected that WBV will not change dyspnoea from baseline. To allow sample size calculation therefore, data of functional performance variables were considered primary and used to estimate sample size. The selected dependent variables were sourced from a previous study of WBV and healthy community-dwelling older adults [25]. Sample size needed for a one tailed paired *t*-test with α 0.05 and *n* = 14 with power = 0.90 was *n* =16 for the 5 chair stands test *n* < 10 for the timed up and go test. To allow for an anticipated participant drop out of at least 20%, a total of 20 participants will be included in the study.

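### Every participant takes WBV first and PLACEBO second, so the WBV–PLACEBO contrast is confounded with period and efficacy is not identified

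*Protocol article*

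**What the plan says.** Methods/design states the design openly: "This trial will be conducted as a non-randomised intervention with crossover to placebo". The Interventions section then fixes one sequence for everyone: "participants will be first allocated to a six-week WBV intervention, a two-week washout period [37], and a six-week PLACEBO intervention". No second sequence appears in the article.

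Methods/design gives these reasons:

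- Phase of the trial: "this trial will be a phase II efficacy trial and as such will not be conducted as a randomised controlled trial".
- Numbers: WBV is placed first "in an effort to maximise participant numbers in the WBV group, with anticipated dropout over the course of the 14-week intervention".
- Compliance and need: "A control condition could compromise trial compliance and randomisation is not critical to an efficacy trial".

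The Objective section says the trial is meant "to test the efficacy of a WBV intervention to beneficially effect exercise tolerance and functional performance of the lower limbs without causing exacerbations".

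The Sample size calculation opens "Sample size needed for a one tailed paired" *t*-test, with α 0.05 and power 0.90. It arrives at 16 participants for the chair-stands test and 20 after allowing for at least 20% dropout. It does not say which two measurements form the pair. The Outcome measures section schedules data collection at baseline and every fortnight to week 14, which is eight occasions.

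**The concern.** In a one-sequence crossover, treatment and period are the same variable. Whatever differs between weeks 0–6 and weeks 8–14 for reasons other than WBV enters the WBV–PLACEBO difference. Candidates are practice on timed tests that are repeated fortnightly, season, the course of COPD, WBV effect that outlasts the washout, and selective loss of participants before PLACEBO begins.

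The direction cannot be known in advance. If end-of-period levels are compared, practice favours the later period, PLACEBO. If within-period changes are compared and practice gains flatten with time, practice favours the earlier period, WBV.

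The stated reasons do not answer this. Being phase II, or studying a disease with exacerbations, does not remove a period effect. An efficacy claim is a causal claim and needs a fair comparison. Protecting WBV numbers against dropout is a genuine consideration, but its size has to be weighed against what it gives up. At stake is whether any result, positive or negative, can be attributed to WBV.

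**Working it through.** **1. The plan's own figure.** 16 / (1 − 0.20) = 20, which matches the stated total. The 16 itself cannot be rebuilt, because no effect size or SD is given. Solving P[t′₁₅(d√16) > t₀.₉₅,₁₅] = 0.90, where t′ is noncentral t, gives an implied standardised paired difference d ≈ 0.767.

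**2. What each design estimates.** Let τ be the WBV–PLACEBO effect, π the period-1-minus-period-2 effect, and λ_W and λ_P the carry-over from WBV and from PLACEBO into the next period.

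- Fixed order: expected difference = τ + π − λ_W. This is one equation, and τ cannot be separated.
- Random order, WBV first: τ + π − λ_W. PLACEBO first: τ − π + λ_P. Half the sum is τ − (λ_W − λ_P)/2. The period effect cancels; unequal carry-over does not.

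**3. What a period shift would do.** The shifts are assumptions, in SDs of the paired difference; the article gives no SD. With n = 16 and one-sided 5%, P(reject) = P[t′₁₅(4δ) > t₀.₉₅,₁₅], where δ is the net standardised shift.

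| Assumed shift | No WBV effect, shift towards WBV: P(reject) | True d = 0.767, shift against WBV: power |
|---|---|---|
| 0 | 5.0% | 90.0% |
| 0.2 SD | 18.9% | 69.9% |
| 0.3 SD | 30.9% | 55.5% |

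**4. The other reading of the test.** If the pair is baseline and end of WBV, PLACEBO does not enter. The table does not apply as framed, but the test is then an uncontrolled before-after comparison and still cannot separate WBV from time.

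**5. Cost of randomising the order.** Let S(t) be the share still in the trial at week t, with N = 20 and the same dropout in both orders. The timing of dropout is not given.

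- WBV completers, fixed order: 20·S(6).
- WBV completers, random order: 10·S(6) + 10·S(14).
- Cost: 10·[S(6) − S(14)].

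With 20% dropout spread evenly, S(6) = 1 − 0.2 × 6/14 = 0.914 and S(14) = 0.80. Completers are 18.3 (fixed) and 17.1 (random), a cost of 1.1. A constant dropout rate gives 18.2 and 17.1, also 1.1.

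The extremes follow from the same formula. If all dropout falls before week 6 the cost is 0; if all falls later it is 10 × 0.20 = 2. At 30% dropout the range is 0 to 3, with 1.6 to 1.7 under steady dropout.

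Participants completing both periods: 20·S(14) = 16 under either order.

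**6. Power with a period term.** With 16 completers split evenly, precision is unchanged and one degree of freedom is lost (14 instead of 15). At d = 0.767 power is 0.898 instead of 0.900.

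**The case against.** The strongest defence is that the trial is small, is labelled phase II, discloses its order plainly and is meant to inform further research. Several parts of that defence stand.

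- The Sample size section does not name the pair. On the baseline-to-end-of-WBV reading, putting WBV first does keep about one more analysable participant (18.3 against 17.1). A reader might infer that the order never helps the analysable number; that is true only for the WBV–PLACEBO pair.
- A reader might infer that nothing about period effects can be learned. That goes too far. The fortnightly data include weeks 6 and 8, so they say something about level shift and residual WBV effect before PLACEBO starts. Comparing within-period changes removes a constant shift, and the test-retest-retest work may blunt early learning. What remains confounded is a time trend of unknown shape.
- The control condition mentioned in the rationale may mean a no-treatment control rather than PLACEBO. The compliance argument is then not self-contradictory, but it has no bearing on the order of two interventions that everyone receives.
- Starting on PLACEBO might change retention. The article gives no data on this, so equal dropout in both orders is an assumption.

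None of these points makes a single sequence able to separate treatment from period.

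**Conclusion.** The point holds. With one sequence the WBV–PLACEBO contrast is confounded with period, and on the alternative reading of the t-test the comparison is uncontrolled. The efficacy objective is not identified on either reading, and no later analysis plan can repair this. The clause calling randomisation not critical is unsound as a justification.

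The error rates of 19% and 31%, and the fall in power to about 56%, show sensitivity to assumed shifts of 0.2 and 0.3 SD. They are not estimates of this trial's bias, whose size and direction are unknown. The cost of about 1.1 WBV completers rests on 20% dropout spread evenly. The plan says at least 20% and gives no timing, so the cost is better read as 0 to 2, or 0 to 3 at 30%.

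Two stronger readings are not supported. The article does not contradict itself: the order is stated consistently and openly, so this is a weak design choice with a poor rationale. Nor would randomising the order cure everything, since unequal carry-over would remain.

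**What to change.** Randomise the order 10:10 (WBV–PLACEBO or PLACEBO–WBV), concealed until after baseline, and analyse the WBV–PLACEBO difference with a period term. State that this balances period effects but that unequal carry-over still rests on the two-week washout. State which two measurements the paired test compares.

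If the order must stay fixed, limit the conclusion to uncontrolled change during WBV, and do not present the WBV–PLACEBO contrast as evidence of efficacy.

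In either case, strike the clause on randomisation from the Methods/design rationale.

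Beyond the WBV completers lost, the cost is an ethics and registry amendment, a 20-line allocation list, and scheduling of the two platforms (the article does not say how many of each exist). The explanation given to participants in the PLACEBO intervention section must also be reworded, because it describes PLACEBO by contrast with a WBV phase already received. No extra participants or visits are needed.

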### Participants and recruitment

Community-dwelling patients listed on the Department of Respiratory and Sleep Medicine, Monash Medical Centre, Southern Health data-base will be contacted to procure interest in participation and later provide informed voluntary consent. Participants must be over 40 years of age, be fully independent in residence, and have well-managed, stable Stage II COPD according to the Global initiative for chronic Obstructive Lung Disease (GOLD) criteria. A convenient sample of people with stable Stage II COPD will be targeted due to a reduced chance of participant dropout from exacerbations independent of the 14-week intervention. Participants must be free of contraindicators to physical activity as well as contraindicators to WBV (free of self reported; vascular disease, reactive arthritis, vertigo, and risk of thromboembolism [28,35,36]. The trial has the ethical approval of the Monash Medical Centre, Southern Health Human Research Ethics Committee A and the Australian Catholic University Human Research Ethics Committee. The trial is registered with the Australian New Zealand Clinical Trials Registry (ACTRN12612000508875).

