### WBV intervention

The WBV intervention will consist 12 WBV sessions over a consecutive six-week period. The participants will complete two vibration sessions per week separated by at least 48 hours. Efficacy of session frequency had been previously established for healthy community-dwelling older adults [25]. A WBV session will consist of five, 60 second vibration bouts, interspersed with 60 seconds of passive rest. Although the most effective protocol is yet to be established, the selected protocol had been used previously to establish efficacy of WBV interventions [36,38,39]. During rest, the participant will remain on the vibration platform and will be encouraged to stand with a posture that resembles the ‘anatomical position’. More specifically, the participant assumes a standing position with the feet together, the arms to the side, and the head, eyes and palms facing forwards. The forearms are supinated.

A side alternating vibration platform (Amazing Super Health, Melbourne, AUS) will be used. For each vibration bout, platform frequency will be 25 Hz, peak-to-peak displacement 2.0 mm, peak acceleration ~24.67 m.s^-2^, and gravitational force ~2.52 *g*. The WBV intensity was chosen to reduce the risk of fracture to fragile bones [40] and potential for other injury [41]. The vibration platform peak-to-peak displacement and frequency were validated prior to this proposal in an unpublished pilot study. Foot placement (second toe) will be equidistant, 20 cm from axis of rotation. The participant will wear flat soled shoes. Skidding will be checked according to the recommended method of the International Society of Musculoskeletal and Neuronal Interactions. A piece of paper will be placed under the foot during a vibration bout to ensure constant contact with the vibration platform [42]. The participant will be required to stand with ~20º knee flexion to allow transmission of vibration about the lower limbs [43]. Knee angle will be filmed, and later quantified across the intervention for each participant.

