## Discussion

Whole-body vibration is a mode of physical activity thought to affect the musculoskeletal, endocrine and cardiovascular systems of the human body. Researchers can choose to use several platform types, a range of vibration frequencies, peak-to-peak displacements and a multitude of stance postures to affect dependent variables. As such, both effective and ineffective results from WBV have been reported. However, negative effects of WBV are rarely reported when vibration platforms and protocols are matched to a specific population [49]. Considering the growing WBV literature base, it is an oversight that prescription guidelines for safe and effective WBV have not been established, despite increasing existence of vibration platforms in the health and fitness industry. However, since many variables of a WBV intervention can be manipulated, comparison among studies and subsequent guideline recommendations are difficult.

Although WBV has rarely been used as an exercise intervention for people with sub-optimal health, condition specific exercise is possible. Whole-body vibration had limited use as an exercise intervention for people with COPD. However, from the paucity of available literature base on sub-optimal health samples, WBV exacerbations are rarely described, but may lack full disclosure.

A WBV intervention should be safe and valid before implemented to a sample cohort, regardless of health status. Encouragingly, WBV did not negatively affect people with stable COPD [34], people with cystic fibrosis [31] or heart transplant recipients [50]. Despite current knowledge of WBV, as a standalone home-based mode of physical activity, efficacy has not been established for improvement or maintenance of exercise tolerance and functional performance of the lower limbs of people with COPD. Furthermore, it is unknown if a long-term WBV intervention will elicit exacerbations of COPD, or be well tolerated and complied by people with COPD.

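### Freedom from contraindications to vibration is defined by self-report alone in the article, so a patient with an actual but unreported contraindication would meet the criterion

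*Protocol article*

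**What the plan says.** The protocol article, under Participants and recruitment, sets two related requirements in one sentence: "Participants must be free of contraindicators to physical activity as well as contraindicators to WBV". The second is spelled out in brackets as being "free of self reported; vascular disease, reactive arthritis, vertigo, and risk of thromboembolism". For the first, contraindications to physical activity, no method of ascertainment is given.

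The same section describes one recruitment route: "Community-dwelling patients listed on the Department of Respiratory and Sleep Medicine, Monash Medical Centre, Southern Health data-base will be contacted".

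The Objective places the exposure outside the clinic: "The intervention will be conducted and data collected in the home of each participant". The section on the WBV intervention gives the amount: "The WBV intervention will consist 12 WBV sessions over a consecutive six-week period". The Discussion sets a general standard: "A WBV intervention should be safe and valid before implemented to a sample cohort, regardless of health status".

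**The concern.** Self-report suits conditions that a patient can feel or has been told about. Two of the four listed items do not fit that description reliably. Thromboembolism risk is a state usually judged from history and clinical data. A patient may report a past event, but may not know that he or she is at risk. Vascular disease may be undiagnosed, or known to the patient under another name.

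Because the wording ties the criterion to what is reported, an unreported condition does not exclude, even where the patient's record documents it. What is at stake is participant safety: such a patient would qualify for repeated vibration although the protocol itself lists the condition as a contraindication. No power, alpha or sample-size figure is affected.

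**Working it through.** The plan states no figure on this point, so there is none to reproduce. The check is a reading of the relevant sections together.

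1. **Is self-report stated or inferred?** It is stated. Participants and recruitment attaches it directly to the vibration list. The point therefore rests on the article's own rule and not on an omission.

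2. **Does the article name any other check on this list?** No. It mentions no record review, clinician confirmation or examination for these four conditions. The GOLD stage and stability requirements concern COPD and not these conditions.

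3. **Does each item suit the method?**
   - Vertigo: a symptom, so self-report is reasonable.
   - Reactive arthritis: a diagnosis that the patient may well know.
   - Vascular disease: may be unknown to the patient or not recognised under that name.
   - Thromboembolism risk: a risk state and the weakest fit.

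4. **What follows under the literal rule?** A patient who has a listed condition and does not report it is free of the self-reported condition, meets the criterion and is formally eligible.

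5. **What exposure follows?** Two sessions per week × 6 weeks = 12 sessions, which agrees with the stated total. Each session has five 60-second bouts, so 12 × 5 × 1 minute = 60 minutes of vibration in all, delivered in the home.

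6. **Is confirmation feasible?** Probably. The only recruitment route described is a hospital department's database, so candidates are already known to a clinical service. The article does not describe what the database contains, so it cannot be said that the database itself holds the needed information.

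7. **How many participants are affected?** The number wrongly admitted depends on the prevalence of the conditions among candidates and on the share that self-report misses. The documents give neither, so no number can be derived.

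**The case against.** The strongest reply is that this is a journal article condensing a fuller protocol that is not shown. Screening procedures such as record review are often left to that document, and the article does not say that records go unchecked. This stands in part: self-report is the only method *this article names*, and a fuller protocol could add a medical check. It does not dispose of the point, because the article chose to specify a method, and the method it specified is self-report.

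Second, other safeguards exist. The requirement on contraindications to physical activity may catch some of the same patients, and the WBV intervention section says that the intensity was chosen to limit fracture and other injury. Both are fair. However, no method is given for the first, and the second does not identify patients with a vascular or thromboembolic contraindication.

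Third, patients can report a previous clot or anticoagulant use, and the cited sources may define the items more closely. That narrows the gap for thromboembolism risk but does not close it for those unaware of their risk.

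Fourth, two ethics committees approved the trial, and self-reported screening is a legitimate design choice. Agreed: this is an improvement to the plan and not the correction of an error.

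A reader might also infer more than the text supports:
- *That ineligible patients will be treated.* Under the literal criterion they are eligible. The accurate description is patients with an actual but unreported contraindication, and their enrolment is a possibility that has not been shown.
- *That the trial's conclusion on tolerability would be distorted.* The listed outcomes are dyspnoea, heart rate, saturation, chair stands, timed up and go, and gait, and the safety element of the objective concerns exacerbations. A vascular or thromboembolic event enters none of the listed outcomes, so that effect is speculative.
- *That the Discussion's remark on safety contradicts the screening rule.* It is a general statement about the intervention and says nothing about how eligibility is ascertained.

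**Conclusion.** The point holds in a limited form. The article defines freedom from contraindications to vibration by self-report, a method that fits at least one listed item poorly and another imperfectly. A patient with an actual but unreported contraindication would meet the criterion and receive the full home vibration course. The size of the problem is unknown, and any count out of 20 would reflect only the assumptions put in.

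The conclusion rests on two assumptions: that the article's wording reflects the screening actually planned, and that the unspecified check on contraindications to physical activity does not already cover the same conditions fully. If a record check is already planned, one clarifying clause settles the matter. The point is a low-cost safety improvement and changes no statistical figure.

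**What to change.** Leave the four listed criteria as they are and change only how they are verified. In Participants and recruitment, replace the self-report wording with: *self-reported and confirmed against the hospital record or by the treating clinician before the first WBV session*. Add consent wording that permits access to the record. If such a check already exists in the full protocol, say so in the article.

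The cost is a short record check for each candidate, the consent wording, and possibly a few more screen failures on the way to 20 participants.

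The check belongs before the first WBV session only. Repeating it before the PLACEBO period would serve little safety purpose, since the stated displacement there is about 0.0 mm. It could also remove participants from the second period alone, causing selective loss in a fixed-order design that was sized on a paired test.
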